## Abstract

**Introduction:**

Exposure to secondhand smoke (SHS) increases children’s risk of acquiring chest and ear infections, tuberculosis, meningitis and asthma. Smoking bans in public places (where implemented) have significantly reduced adults’ exposure to SHS. However, for children, homes remain the most likely place for them to be exposed to SHS. Additional measures are therefore required to protect children from SHS. In a feasibility study in Dhaka, Bangladesh, we have shown that a school-based smoke-free intervention (SFI) was successful in encouraging children to negotiate and implement smoking restrictions in homes. We will now conduct a pilot trial to inform plans to undertake a cluster randomised controlled trial (RCT) investigating the effectiveness and cost-effectiveness of SFI in reducing children’s exposure to SHS.

**Methods and analysis:**

We plan to recruit 12 primary schools in Dhaka, Bangladesh. From these schools, we will recruit approximately 360 schoolchildren in year 5 (10–12 years old), that is, 30 per school. SFI consists of six interactive educational activities aimed at increasing pupils’ knowledge about SHS and related harms, motivating them to act, providing skills to negotiate with adults to persuade them not to smoke inside homes and helping families to ‘sign-up’ to a voluntary contract to make their homes smoke-free. Children in the control arm will receive the usual education. We will estimate: recruitment and attrition rates, acceptability, fidelity to SFI, effect size, intracluster correlation coefficient, cost of intervention and adverse events. Our primary outcome will consist of SHS exposure in children measured by salivary cotinine. Secondary outcomes will include respiratory symptoms, lung function tests, healthcare contacts, school attendance, smoking uptake, quality of life and academic performance.

**Ethics and dissemination:**

The trial has received ethics approval from the Research Governance Committee at the University of York. Findings will help us plan for the definitive trial.

**Trial registration number:**

ISRCTN68690577.

Strengths and limitations of this studyA pilot to inform the parameters required for a pioneering trial to test the effectiveness and cost-effectiveness of a school-based behavioural change intervention aimed at children to negotiate and implement smoking restrictions in homes.A pilot that is rooted in a well-developed smoke-free intervention (SFI) that has shown promising results from the feasibility study in Dhaka, Bangladesh.The first study of secondhand smoke (SHS) exposure in children that will assess a variety of clinical, behavioural and school performance-related outcomes (in children), such as the frequency and severity of respiratory illnesses, healthcare contacts, school absenteeism, smoking uptake and improvements in their lung function, quality of life and academic performance.The only limitation is that the trial is not powered to show the effectiveness of the SFI, which can be attributed to its design being a pilot trial to inform plans of a bigger definitive cluster RCT in the future.

## Introduction

Secondhand smoke (SHS) contains an estimated 4000 toxic chemicals and is a serious health hazard to non-smokers. Every year, an estimated 600 000 people die due to SHS exposure.^1^ Exposure to SHS is particularly harmful to children's health and increases their risk of acquiring lower respiratory tract and middle ear infections,^2–4^ invasive meningococcal disease,^5^ tuberculosis^6^
^7^ and incident cases, recurrent episodes and increased severity of asthma.^8^ Parental smoking is also associated with their children's admissions to hospitals.^3^ Children living in smoking households are at risk of poor general and functional health,^9^ lower academic performance,^10^ and a high smoking uptake in later life.^11^

Recognising SHS as a public health threat, most countries have introduced comprehensive smoking bans in enclosed public and workplaces. This has, in countries where these bans are strictly enforced, significantly reduced exposure to SHS and its associated morbidity and mortality.^12^ However, for most non-smoking women and children, homes and cars remain important sources of SHS exposure. Additional measures are therefore required to protect non-smokers, particularly children, from SHS exposure. In Bangladesh, exposure to SHS has been recognised as a particularly serious threat to children's health given the high prevalence of smoking by male adults.^13^ However, smoking bans in public and workplaces are only partially implemented and little has been done to protect children from exposure to SHS at home. We carried out a recent household survey that revealed that most households (56%) have at least one smoker and that smoking indoors in front of children (40%) was a common practice.^14^

The evidence for the effectiveness of interventions to provide children a smoke-free environment at home is scarce. A recent Cochrane review concluded that, despite several studies on parental education and counselling programmes, their effectiveness in reducing children’s tobacco smoke exposure has not been clearly demonstrated.^15^ An alternative approach, for which there is also only very limited research, is to encourage children themselves to negotiate smoking restrictions in their households.^16^ We developed a school-based SFI and found through a feasibility trial in Dhaka, Bangladesh (24 schools, 781 children) that it was acceptable and successful in getting children to negotiate implementation of smoking restrictions at home (OR 3.9; 95% CI 2.0 to 7.5).^17^ Schools were also willing to participate and be randomised in a trial. Encouraged by these findings, we now wish to assess if the success of this intervention also translates to reduce SHS exposure in children and improves their health outcomes and academic achievements.

The principal question for our planned follow-on definitive trial is: What is the effectiveness and cost-effectiveness of a school-based SFI in reducing children's exposure to SHS (primary outcome), the frequency and severity of respiratory illnesses, healthcare contacts, school absenteeism, smoking uptake and in improving their lung function, quality of life and school performance?

Prior to conducting a definitive trial to answer the above question, we wish to first conduct a pilot trial that informs the parameters required for conducting the definitive trial.^18^ Our *specific research questions* for this pilot study are therefore to ascertain:
What are the recruitment and attrition rates for schools (clusters) and children?What is the feasibility and acceptability of measuring the primary and secondary outcomes?What is the likely effect size and its variance in relation to the primary outcome measure?What is the intracluster correlation coefficient (ICC) among children for the trial outcomes?What is the fidelity of delivering SFI in schools?What are the costs associated with delivering SFI through schools?What would facilitate and hinder in scaling up SFI in schools and their curriculum?What is the frequency and nature of any adverse events (AE)?

## Methods and analysis

This is a two-arm pilot cluster randomised controlled trial (RCT) of SFI with an embedded preliminary health economic analysis and a qualitative evaluation. This is a 2-year study. We will recruit participants (schools and children) and start baseline assessments in the first 3 months. Between months 3 and 6, we will complete all baseline assessments, randomise schools and start delivering the intervention. We expect respective schools to have delivered the intervention by month 9, which means that all follow-ups will be completed between months 18 and 21. We will complete the analysis in the last 3 months and submit our final report at the end of 2 years.

### Study sites

The study will be conducted in Mirpur and Savar areas of Dhaka Division, Bangladesh. According to the 2011 census, these two sites geographically typify urban and peri-urban contexts, respectively, with a population of more than a million in each area. Mirpur is a typical densely populated urban area in Dhaka with the majority of its population dependent on non-agricultural livelihood and with access to amenities such as paved road, electricity, gas, water supply and drainage systems. On the other hand, Savar is a peri-urban area located 24 km northwest of Dhaka. The majority of its population is dependent on agriculture and industry located around Dhaka. These two areas have been chosen for their typical demographic and socioeconomic structures and existing links with the local communities, schools and health facilities.

### Study clusters (schools)

We will recruit 12 schools from the above two sites, six from each area. The key eligibility criteria are as below.

#### Inclusion criteria (schools)

We will include both public and private schools if they:
Follow mainstream curricula approved by the educational authorities.Have year-5 classes, with >40 and <120 year-5 children (10–12 years old) per class.Have a ‘no-smoking’ policy and all participating year-5 teachers are self-reported non-smokers. It would be desirable to exclude those schools that have any year-5 teachers who smoke. However, given the difficulty in verifying smoking status, we will not make this a mandatory exclusion criterion.

#### Exclusion criteria (schools)

We will exclude schools if they:
Have only primary school classes—these will be excluded due to the challenges of following up children as they move to a secondary school in year 6.Teach in English medium rather than in Bangla—such schools are in a minority in Bangladesh and usually cater for children from affluent backgrounds. There will be very few such schools in our proposed study sites.Have already received training on SFI in a previous project, unless the teachers who were trained have left the school.Are religious or faith-based schools not following the prescribed curricula.

#### Identifying and recruiting eligible clusters (schools)

We will survey the study sites and prepare a list of schools containing information on their class sizes in year 5, primary or secondary school status, public or private status, co-education or single sex schools and their medium (language) of teaching. Schools will be assessed for eligibility, using the criteria stated above. Once found eligible, these will be approached for recruitment. We acknowledge that some of the eligibility criteria can only be assessed after approaching schools and talking to the headmaster and year-5 teachers.

Those schools identified and found eligible on the basis of the available information will be sent a letter addressed to the head teacher, including brief information about the trial and inviting the school to take part in the trial. We will offer to meet head teachers face to face to provide verbal information and responses to their queries. We will also explain random allocation. Interested schools will be provided with a detailed information sheet.

Those who are not eligible or who meet the eligibility criteria but do not agree to participate after receiving the trial information will not be enrolled in the trial. However, their reasons for not meeting the eligibility criteria or declining to participate will be recorded.

Once recruited, we will endeavour to keep all schools on board and included in the study. If, for any reason, a school withdraws before randomisation, we will recruit a new school to replace the withdrawing school. However, if the withdrawal takes place after randomisation, we will not replace such a school and will include it in our analyses.

### Study participants (children)

We will recruit 360 year-5 (ie, at least 30 from each school) schoolchildren (10–12-years) after seeking their parents’ consent and their assent through schools. Being the oldest year in primary school years, we consider this year to be the optimal age group to understand the message and engage with their family members to implement smoking restrictions. The key eligibility criteria are as below.

#### Inclusion criteria (children)

We will include children if they are:
Studying in year-5 in the participating school and their age range is between 10 and 12 years;Self-reported non-smokers.

#### Exclusion criteria (children)

We will exclude children if they have any of the following conditions/situations that the school is aware of:
Physical or mental disabilities;Learning difficulties and/or special learning needs;Behavioural problems and/or conduct disorder;Serious medical condition which is either life-threatening or requires regular hospitalisation.

#### Identifying, recruiting and consenting eligible participants (children)

We will request schools to prepare a list of eligible children including all those who meet the inclusion criteria and excluding all those who fall into the exclusion criteria list. Once an eligibility list is prepared, we will give all schools the required number of trial information packs to proceed with the recruitment.

All children participating in this trial will be under 16 years and therefore parental/carer consent is required for them to take part. On the basis of our experience of conducting a previous study in schools in Bangladesh (approved by a national ethics committee) and advice received from a number of academics who work in schools in the UK, we will obtain parental consent on an opt-out basis as follows. The participating schools will send out the trial information packs to parents of all eligible children, containing an information sheet, and a parent/carer opt-out consent form. We will ask parents/carers to discuss the trial with their child/children. If either the parents or children are unwilling or unable to participate in the trial, we will ask the parents to indicate this by either sending us an opt-out consent form in a self-addressed prepaid envelope or calling/texting/emailing us on the contact details provided within the information pack. We will give parents/carers a minimum period of 7 days to indicate if they do not wish their child(ren) to take part in the study.

Moreover, at the time of recruitment, children will be of an age (10–12 years) where they are able to understand their potential involvement in research and can make an informed decision. Children will therefore be provided with an age appropriate information sheet, which will be given out to them at school. If children are unwilling, they can either let their teachers or parents know, as they feel appropriate. If parents indicate their disapproval for their child to take part in the study, this will supersede the child's assent to participate. Any child who has, or whose parents/carers have, declined to participate will be taken out from the list of eligible children by the school, and the final list will be handed over to the research team. All participating children will be given an enrolment number (including a code for school), which will be recorded on the final list of eligible children, printed on all enquiry tools and entered in the database.

Those children who do not meet the eligibility criteria, or those who meet the criteria but either their parents or they would not agree to participate after receiving the trial information, will not be enrolled in the trial. However, their reasons for not meeting the eligibility criteria or declining to participate will be recorded. This information will be kept completely anonymous.

A child can be withdrawn from participation at any time after enrolment or allocation. If a child is withdrawn from the intervention for any reason, their follow-up assessments and data collection will continue as per protocol unless the parents/carers or child specifically asks for their withdrawal from the study completely. However, if the child is withdrawn completely from the study, then no more data will be collected. They will still be included in the analysis and counted as lost to follow-up. The information already collected will be kept in the database unless the parents/carers or child specifically asks for their information to be removed.

### Cluster (schools) randomisation and allocation

Once the necessary baseline data have been logged into a database, the participating schools will be randomly allocated to each of the two arms, intervention and control, on an equal basis (ie, six schools in each arm). Each intervention school will be paired with a control school for follow-up purposes. We will use a restricted method of allocation called minimisation, which achieves balanced groups efficiently. For this, we will use three criteria, public/private status of school, boys to girls’ ratio, and mean number of children exposed to SHS at baseline.

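### Schools are recruited six per area, but area is not a minimisation criterion, so an uneven urban/peri-urban split between arms is about as likely as not

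*Protocol article*

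**What the plan says.** All references are to the protocol article.

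- **Study clusters (schools)** sets the only recruitment quota for schools: "We will recruit 12 schools from the above two sites, six from each area".
- **Study sites** says that "these two sites geographically typify urban and peri-urban contexts, respectively". Mirpur is described as densely populated, with non-agricultural livelihoods and access to paved roads and utilities. Of Savar it says: "The majority of its population is dependent on agriculture and industry located around Dhaka".
- **Cluster (schools) randomisation and allocation** assigns six schools to each arm once baseline data are in the database. On method: "We will use a restricted method of allocation called minimisation, which achieves balanced groups efficiently". On the factors: "For this, we will use three criteria, public/private status of school", then the ratio of boys to girls, and "mean number of children exposed to SHS at baseline". Area is not among them, and no stratification by area is mentioned.
- The same section pairs each intervention school with a control school, but only for follow-up. It does not say that the pairs lie within an area.

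**The concern.** The design fixes the area mix of the whole sample but leaves the area mix of each arm to chance. With only 12 schools, chance can leave the arms clearly uneven.

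Area is a plausible source of outcome differences. The list of confounding variables includes household amenities, built environment, neighbourhood and cooking with gas, which are the kind of features used to describe the two sites. Balancing baseline exposure deals with what acts through exposure. Lung function, symptoms, health service use, absenteeism and academic performance could differ by area for other reasons.

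Two things are at stake:

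- **The arm difference.** The statistical analysis section will report differences between arms with 95% confidence intervals, and the effect size and its variance are stated pilot questions for planning the definitive trial.
- **The implementation data.** Fidelity scores, delivery costs and the teacher interviews come from the six intervention schools. If five of these are in one area, the other area contributes one school. No later adjustment can restore that information.

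**Working it through.** **Inputs.** 12 schools, six per area (Study clusters); six schools per arm and three criteria without area (Cluster randomisation and allocation); two teachers and one head teacher interviewed per intervention school (Qualitative evaluation). The plan gives no figure for area balance, so there is none to reproduce.

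**Step 1: chance of each split.** Suppose the three criteria are unrelated to area. The number of Mirpur schools in the intervention arm, k, then has probability C(6,k) × C(6,6−k) / C(12,6), with C(12,6) = 924.

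| Split within each area | Allocations | Probability |
|---|---|---|
| 3:3 | 20 × 20 = 400 | 43.3% |
| 4:2 | 2 × 15 × 15 = 450 | 48.7% |
| 5:1 | 2 × 6 × 6 = 72 | 7.8% |
| 6:0 | 2 × 1 × 1 = 2 | 0.2% |

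Hence 4:2 or worse is 524/924 = 56.7%, and 5:1 or worse is 74/924 = 8.0%.

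**Step 2: does minimisation change this?** A simulation minimised 12 schools to 6:6, with 20,000 runs per setting. Its assumptions are not in the protocol: three two-level factors, assignment to the better arm with probability 0.8 or 1.0, and each factor copying the school's area with the probability shown.

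| Copy probability | 4:2 or worse | 5:1 or worse |
|---|---|---|
| 0 (unrelated) | 56.7% | 7.7–8.3% |
| 0.3 | 51–54% | 5–6% |
| 0.6 | 35–43% | 1–2% |

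Minimising on factors unrelated to area gives no protection for area. Factors that track area give some.

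**Step 3: cost to precision.** With six schools per arm and per area, the correlation between arm and area is (a² − b²)/36 for an a:b split.

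- 4:2: (16 − 4)/36 = 1/3
- 5:1: (25 − 1)/36 = 2/3

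Adjusting for area multiplies the variance of the arm estimate by 1/(1 − r²), relative to a 3:3 split.

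- 4:2: 1/(1 − 1/9) = 1.125, about 1.13
- 5:1: 1/(1 − 4/9) = 1.8

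This assumes equally weighted schools and the same residual variance in each case. Without adjustment, the same fractions (one third and two thirds) of any true area difference enter the observed arm difference in that particular allocation. The documents give no size for an area difference, so none is attached here.

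**Step 4: implementation data.** Interviews total 6 × 3 = 18. At 5:1, one area supplies 1 of 6 intervention schools and 3 of 18 interviewees.

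**Step 5: the exposure criterion.** A mean number is unclear for a single school. Read as a count, it depends on enrolment as well as on exposure. The plan is for at least 30 children per school and 360 in all. Since 12 × 30 = 360, schools would be nearly equal in size, and count and proportion would rank them almost alike.

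**The case against.** The case against giving this much weight is a fair one.

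- **It is a pilot.** It is not powered for effectiveness, and comparing the arms is expressly not its purpose. Recruitment and attrition rates hardly depend on area balance between arms. This stands and limits the impact.
- **Baseline exposure is already balanced.** It is the criterion closest to cotinine, so area differences acting through exposure are partly controlled. This also stands, though less so for the other outcomes.
- **The analysis may adjust for area.** That may be specified in an analysis plan that is not shown. It would deal with confounding in the realised allocation, but at the variance cost in step 3, and it would not help the implementation data.
- **Which few factors to balance with 12 clusters is a judgement.** True; but area is the one feature for which the design already sets a quota.

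A reader might also infer stronger points that the documents do not support:

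- *The allocation biases the trial.* It does not. Imbalance in either direction is equally likely, so the expected error is zero.
- *Imbalance inflates between-school variance and so the intracluster correlation.* Within an arm, an area difference d contributes p(1−p)d²: 0.250d² at 3:3, 0.222d² at 4:2 and 0.139d² at 5:1. Imbalance lowers this component. What rises is the sampling variance of the arm difference.
- *The areas were chosen because they differ.* The Study sites section gives typical structures and existing links as the reasons, and no stated research question contrasts the areas.
- *Imbalance upsets the pairing of schools.* The pairing is only for follow-up, and nothing requires pairs within an area.

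**Conclusion.** The point holds as a modest design weakness. Nothing stated in the protocol keeps the urban and peri-urban schools balanced between arms. An uneven split has a probability of 57% if the criteria are unrelated to area, and roughly 35–54% under the assumed degrees of association in step 2. A split of 5:1 or worse has a probability of 8%, falling to about 1–6% under those assumptions.

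The consequence is lost precision in the preliminary arm difference and, in the rarer extreme splits, thin implementation data from one area. It is not systematic bias, and it invalidates no confirmatory test, because none is planned. It still deserves attention before allocation, since the area split cannot be changed once schools are assigned. The wording of the exposure criterion is a minor clarification only.

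**What to change.** In the section on cluster randomisation and allocation, state that allocation is stratified by area, with three schools per arm in Mirpur and three per arm in Savar, and that the existing criteria are applied within each area. This gives 3:3 with certainty and preserves six schools per arm. It is feasible because allocation follows the logging of baseline data.

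The lesser option is to add area as a fourth minimisation factor. Under the simulation assumptions in step 2, this lowers 4:2 or worse to about 13–39% and 5:1 or worse to about 0–1.4%.

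The cost is one sentence, a small change to the allocation procedure, and slightly coarser balance on the other three criteria. There is no need to replace minimisation with another method; that would be a matter of preference.

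In the same edit, define the exposure criterion as the proportion of enrolled children in each school who are exposed at baseline.
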